### Randomisation and blinding

Upon completion of all the baseline assessments, consenting participants will be stratified by MRS scores (i.e. 1, 2 and 3) and randomised into two groups; overground walking with paretic lower limb loading or overground walking without paretic lower limb loading in a 1:1 ratio (Fig. 2) by a third party not involved in other aspects of the study. Allocation of participants will be concealed using consecutive numbered, sealed and opaque envelopes prepared using a web-based randomisation tool (available at https://www.sealedenvelope.com) with permuted block size of 6. All outcome assessors will be blinded to participants’ group allocation. However, it will be impossible to blind physiotherapists and participants considering the nature of the study interventions.

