**Methods:**

This is a two-center, single-blind, two-arm parallel randomised controlled trial. Forty-eight stroke survivors with mild to moderate disability will be recruited from two tertiary facilities and randomly assigned into two intervention arms; overground walking with paretic lower limb loading or overground walking without paretic lower limb loading in a 1:1 ratio. All interventions will be administered thrice weekly for 8 weeks. Primary outcomes will be step length and gait speed whereas the secondary outcomes will include step length symmetry ratio, stride length, stride length symmetry ratio, stride width, cadence and motor function. All outcomes will be assessed at baseline, 4, 8 and 20 weeks after the start of intervention.

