### Statistical analysis

Descriptive statistics of mean, standard deviation, percentage and frequency will be used to summarise the data. Comparison of baseline categorical variables among groups will be conducted using Fisher’s exact test or chi-square test and for continuous variables using independent *t*-test or Mann–Whitney *U* test where applicable. Intention-to-treat principle will be used for the primary statistical analysis by including each participant’s available data in accordance with original allocation and irrespective of the level of attendance. The primary and secondary outcomes will be analysed using linear mixed-effects models (LMMs) by including time (4, 8 and 20 weeks, baseline will be the reference), treatment (overground walking with paretic lower limb loading and overground walking without paretic lower limb loading) and a time × treatment interaction as fixed effects, and a random intercept to account for within-subject correlations. Treatment effect will be defined as the adjusted between-group difference and the associated 95% confidence intervals (CI). We opted to use LMMs because it provides unbiased estimates when data are missing at random [59]. Additionally, per-protocol analysis using the LMMs will be performed as sensitivity analysis by excluding randomised participants who did not received allocated intervention, or who attended fewer than 18 treatment sessions, received proscribed concomitant intervention known to influence gait, and experienced exclusionary medical conditions listed in the study exclusion criteria. All the statistical procedures will be performed using SPSS version 23.0 (IBM Co., Armonk, NY, USA) at a probability level of 0.05.

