The present study may further support the evidence of the use of weight loading in gait rehabilitation of stroke patients which may guide clinical practice. A potential limitation of this study is that overground walking on the land-based surface, particularly among older patients and those with excess weight, may increase burden on weight-bearing joints and the risk of falls as compared to underwater treadmill walking. Another limitation is that spatiotemporal gait parameters will not be assessed with gold standard instruments such as three-dimensional (3-D) motion capture system, and electronic walkways, such as GAITRite® [65]. Nevertheless, these instruments are quite expensive to acquire and operate and, as such, the use of technically simple and inexpensive methods like ink footprints may be more feasible for clinical use, especially in resource-constrained settings. Furthermore, because the study will be conducted in two centers, there could be a slight difference in how the therapists perform intervention and assessment.

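### The analysis model leaves out the MRS stratification factor and centre and does not define the treatment contrast; the cost depends on which contrast is meant

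*Protocol article*

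**What the plan says.** **Design.** Protocol article, Randomisation and blinding: "consenting participants will be stratified by MRS scores (i.e. 1, 2 and 3) and randomised into two groups", with a "permuted block size of 6". MRS is the only stratification factor named; centre is not one. The abstract states: "This is a two-center, single-blind, two-arm parallel randomised controlled trial".

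**Centres.** The Discussion lists as a limitation that "because the study will be conducted in two centers, there could be a slight difference in how the therapists perform intervention and assessment".

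**Model.** Statistical analysis fits linear mixed-effects models "by including time (4, 8 and 20 weeks, baseline will be the reference), treatment" and a "time × treatment interaction as fixed effects, and a random intercept to account for within-subject correlations". Baseline is therefore one of the four levels of the response, not a covariate. The same section defines the treatment effect as an adjusted between-group difference with a 95% interval. It names no adjustment covariate, and it does not say whether the effect is the difference at a time point or the difference in change from baseline.

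**The concern.** A model is normally expected to carry the factors that restricted the randomisation. Stratifying by MRS makes the arms more alike on MRS, and a model that ignores MRS gives no credit for this in the standard error. Centre has no protection in either design or model, although the authors themselves expect that it might matter.

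This is more than a detail that an article leaves to a separate analysis plan, because the article lists the fixed effects term by term and the list does not match its own randomisation. With 24 participants per arm, interval width matters. The word adjusted does not settle the matter, since no covariate stands behind it.

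**Working it through.** **1. The plan's own figure.** Sample size calculation gives f = 0.20, alpha 0.05, power 0.80 and correlation 0.5. For the within-between interaction with 3 measurements, lambda = f² × N × m/(1 − rho) = 0.04 × 42 × 3/0.5 = 10.08 on 2 and 80 degrees of freedom, which gives power 0.803. So N = 42 is reproduced (4 measurements would need 36). Then 42 × 1.15 = 48.3, in line with the stated 48. Neither MRS nor centre enters, so this point alters no stated figure.

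**2. Assumptions for the rest.** The article gives no variance explained by MRS or centre, so a range is assumed: shares of total variance, constant over time, outcome SD 1, within-subject correlation 0.5, 24 per arm, complete data.

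**3. Difference at a time point (week 8).** Without adjustment, SE = sqrt(2/24) = 0.289. With a share R² explained, it is roughly 0.289 × sqrt(1 − R²), slightly more after the lost degrees of freedom. Simulation with MRS-stratified blocks of 6 and centre unstratified gave these mean model SEs:

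| MRS + centre share | 0.289 × sqrt(1 − R²) | SE without | SE with | Change |
|---|---|---|---|---|
| 0 + 0% | 0.289 | 0.288 | 0.292 | +1% |
| 10 + 5% | 0.266 | 0.288 | 0.268 | −7% |
| 20 + 5% | 0.250 | 0.288 | 0.252 | −12% |
| 30 + 10% | 0.224 | 0.290 | 0.225 | −22% |

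Part of this is correction of an overstated SE and not new information. At 20 + 5% the unadjusted model SE was 0.288, but the estimates themselves had a simulated SD of 0.271. With MRS exactly balanced the SD would be sqrt(2/24 × 0.80) = 0.258. Omitting MRS is conservative on this contrast.

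**4. Change from baseline (time × treatment).** The variance of a change is 2 × (1 − 0.5) = 1, so the SE is again about 0.289. A time-constant MRS or centre effect is subtracted out within each participant.

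- One complete-data mixed-model fit gave estimate 0.1333 and SE 0.2772 both with and without MRS and centre main effects.
- One fit with 15% dropout gave SE 0.3073 without and 0.3066 with them.
- Adding MRS and centre effects on change raised the SE from 0.287 to 0.291 (about 1%) when the factors do not affect change. It lowered the SE from 0.300 to 0.292 (about 3%) with assumed slopes of 0.2 SD each.

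**5. Chance centre imbalance.** With equal centres (assumed), the arm difference in centre share has SD sqrt(0.25 × 2/24 × 48/47) = 0.146, a 95% range of about ±29 percentage points. Arms differ by 4 or more participants within a centre with probability 0.39 (0.32 for a 12/36 split), and by 8 or more with probability 0.04 (0.02). If the centres differed by 0.5 SD (assumed), the outer 95% limit would move a time-point estimate by 0.286 × 0.5 = 0.14 SD. The same shift reaches a change contrast only if the centres differ by that much in change.

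**6. Baseline as a covariate.** Baseline alone leaves residual variance 1 − 0.5² = 0.75. With MRS and centre explaining a share c as well, it is (1 − c) − (0.5 − c)²/(1 − c): 0.706 at c = 0.15, 0.667 at 0.25 and 0.583 at 0.40. The further cut in SE is 1 − sqrt(0.706/0.75) = 3%, then 6% and 12%, before a small loss for 3 degrees of freedom.

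**The case against.** The strongest reply is that the listed model treats baseline as a response with a random intercept, so on a change-from-baseline reading nothing is lost to time-constant MRS or centre effects. That stands, and step 4 confirms it. A reader might infer that precision and protection are lost whichever contrast is used, or that adjustment is equivalent to a larger trial through 48/(1 − R²). The documents do not support this: that formula belongs to a time-point comparison, and the article does not say that such a comparison is intended.

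A reader might also infer that an unstratified centre biases the result. It does not. Chance imbalance under randomisation is random error, already part of the unadjusted standard error. The article calls the centre difference only possible and slight, and it describes common training of the research assistants with an assessment of their familiarity with the procedures. Not stratifying by centre is itself defensible: 3 MRS levels × 2 centres would give six strata averaging 48/6 = 8 participants with blocks of 6.

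It can also be said that adjusted signals an intention to include covariates that are listed elsewhere. That is possible, but the terms are spelled out and no covariate is among them.

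Two things survive. The contrast is left open, so the time-point reading remains available. And the conceded difference includes how the intervention is delivered. Baseline is measured before randomisation, so a delivery difference would act only on follow-up and would not cancel from a change contrast.

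**Conclusion.** The point holds in limited form. The stated model does not reflect the stated stratification, omits centre, and calls the effect adjusted without naming a covariate or a contrast.

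- **Validity:** omitting MRS does not bias the estimate, and chance centre imbalance is not bias.
- **Time-point contrast:** the SE is about 7 to 22% smaller with both factors if they explain 15 to 40% of total variance, and about 1% larger if they explain nothing.
- **Change contrast:** there is a gain only if MRS or centre affects change, for example SE 0.300 to 0.292; otherwise about a 1% loss.

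The variance shares, slopes, equal centre sizes and centre effect are all assumptions. The change is worth making because it costs little and removes an ambiguity, not because the planned analysis would be invalid.

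**What to change.** In Statistical analysis:

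1. State which contrast, at which time point, is the treatment effect, and what it is adjusted for.
2. Prespecify MRS stratum (3 levels) and centre (2 levels) in the model for all primary and secondary outcomes.
3. Preferably take the baseline outcome as a covariate, model weeks 4, 8 and 20 as the response, and add MRS and centre as main effects. These cost 2 + 1 = 3 degrees of freedom.
4. If baseline stays a response level, add MRS × time and centre × time as well, since main effects alone do nothing for the change contrast. That is 3 main-effect parameters plus 3 × 3 = 9 interaction parameters, 12 in all, with a roughly 1% larger SE if the factors do not affect change.

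MRS is already recorded on the study proforma and the recruiting hospital is known, so no new data are needed. The randomisation and the sample size stay as they are.

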**Fig. 2 Fig2:**
[figure not shown]
Flowchart showing flow of participants through the study

### Study interventions

#### Overground walking with paretic lower limb loading group

Participants assigned to this group will first receive 5 min warm-up, followed by 15 min conventional exercise, 15–25 min overground walking with paretic lower limb loading, and lastly 5 min cool-down. The warm-up and cool-down will be the same and consist of passive stretching to hamstrings and calf muscles, and a range of motion exercise to the lower limbs. The conventional exercise consists of active-assisted exercises (AAEs) to the lower limbs on the mat, followed by strength training such as sit-to-stand and squatting exercises. For the AAE, assistance will be provided manually by an external force (therapist’s hand) when the participants’ muscle strength is inadequate to complete the motion. For the strength training, participants will perform the sit-to-stand exercise using a comfortable chair at their own pace which will be later progressed to squatting exercises by holding a parallel bar.

The procedure for the overground walking with lower limb loading is similar to that described by Abba et al. [48] except for the addition of weight to the paretic lower limb and increase in intensity of walking in the current study. The walking will be conducted on a flat surface of 15 × 10 m dimensions in the physiotherapy gymnasium. Participants will undergo to and fro overground walk with a 1.5-kg sandbag attached to the paretic limb. The 1.5-kg sandbag was chosen based on the findings of our pilot study (unpublished data) conducted on 18 chronic stroke survivors. We found this weight to be the most comfortable and tolerable weight for overground walking among stroke patients who presented with mild to moderate disability based on the scores of the MRS. Prior to the overground walking, participants will be asked to sit in a relaxed position on a chair with their feet on the ground. The selected weight will be strapped 2 cm above the ankle of the paretic lower limb with the malleoli being the reference point [43]. The strapping will be done in such a way that it is not loose or too tight to give discomfort to the participants while carrying out the training. Afterwards, the participants will be instructed to stand and then walk to and fro a 10-m path (within 15 × 10 m dimensions) labeled with adhesive tape to guide the walking in a straight line. Each participant will be instructed to walk with standardised instruction “walk at your normal, comfortable pace” [49] for 5 min after which they will be asked to stop and rest for 2 min. The training will be repeated 3 times in the first 2 weeks of the study (15 min), 4 times in weeks 3–4 of the study (20 min), and 5 times in weeks 5–8 of the study (25 min). Weight will be unloaded from the paretic limb after completing the training session. The participants will be monitored throughout as they carry out the training, and those reporting symptoms of exertional intolerance outside the target zone (i.e. 12–14) on Borg’s rate of perceived exertion (RPE) scale [50] would be terminated at any time. Treatment will be delivered individually, thrice weekly for 8 weeks. The duration of the training session is expected to last from 40 min in the first week to 50 min in the 8th week. Details of the duration and progression of the study interventions are provided in Table 1.

**Table 1 Tab1:** Duration and progression of the study interventions

Week	Frequency per week	Warm-up time (min)	Rest time (min)	Conventional exercise time (min)	Rest time (min)	Overground exercise time (min)	Cool-down time (min)	Total rest time (min)	Total exercise time (min)
1^st^	3	5	2	15	2	15	5	4	40
2^nd^	3	5	2	15	2	15	5	4	40
3^rd^	3	5	2	15	2	20	5	4	45
4^th^	3	5	2	15	2	20	5	4	45
5^th^	3	5	2	15	2	25	5	4	50
6^th^	3	5	2	15	2	25	5	4	50
7^th^	3	5	2	15	2	25	5	4	50
8^th^	3	5	2	15	2	25	5	4	50

#### Overground walking without paretic limb loading group

Participants allocated to this group will undergo the same intervention as described for the overground walking with paretic lower limb loading group except that weight will not be applied to the participants’ paretic limb. Treatment will be delivered individually, thrice weekly for 8 weeks. The duration of the training session is expected to last from 40 min in the first week to 50 min in the 8th week. Details of the duration and progression of the study interventions are provided in Table 1.

### Outcome assessments and follow-ups

The primary outcomes will be step length and gait speed whereas the secondary outcomes will be step length symmetry ratio, stride length, stride length symmetry ratio, stride width, cadence and motor function (Table 2). All outcomes will be assessed at baseline prior to randomisation, 4, 8 and 20 weeks after the start of intervention. All participants will be reminded about thier follow-ups via phone call on regular basis.

**Table 2 Tab2:** Description of primary and secondary outcomes and time points of assessments

S/N	Outcome measure	Description/administration	Psychometrics	Assessment point
	**Primary outcomes**			
1	Step length	It will be measured as the distance from the heel strike of one foot to the heel strike on the next successive step of the opposite foot, using the midpoint of the heel square as the reference point (distance CD measured in cm) See Fig. 3	The measure is easy and has adequate test–retest reliability (*r* = 0.97) [50] and concurrent validity with strobe-light photography [51]	Baseline 4th week 8th week 20th week
2	Gait speed	It will be measured as the distance covered in meters per time taken in seconds to walk a specified distance on a level surface. In this study, it will be calculated as the ratio of 10 m distance per unit time covered during the gait training	The measure has excellent test–retest reliability (ICC = 0.94–0.99) [49, 52] and concurrent validity (*r* = 0.95) with GAITRite system [53]	Baseline 4th week 8th week 20th week
	**Secondary outcomes**			
3	Step length symmetry ratio	It will be calculated by dividing the step length of the paretic limb to that of the non-paretic limb	The calculation has been recommended in determining gait symmetry [28]	Baseline 4th week 8th week 20th week
4	Stride length	It will be measured by taking the midpoint of the heel square as a reference point for measurement, and then measuring the linear distance from the heel strike of one foot to the heel strike of the next successive step of the same foot (distance AB measured in cm). See Fig. 3	The measure is easy and has excellent test–retest reliability (*r* = 0.925) [50] and concurrent validity (*r* = 0.85) with GAITRite system [53]	Baseline 4th week 8th week 20th week
5	Stride length symmetry ratio	It will be calculated by dividing the stride length of the paretic limb to that of the non-paretic limb		Baseline 4th week 8th week 20th week
6	Stride width	It will be measured as the transverse linear distance between points on 2 successive feet. Heel-to-heel step width will be calculated as the difference between distance G and F, measured from the midpoint of 2 successive heel squares of the opposite feet to the edge of the walking path. See Fig. 3	The measure has adequate test–retest reliability (*r* = 0.782) [50] and concurrent validity with strobe-light photography [51]	Baseline 4th week 8th week 20th week
7	Cadence	It will be measured as the number of steps taken per unit time. The value will be calculated by dividing the total number of steps taken on the paper by the total time needed to walk across the length of the floor (measured in steps per minute)	The measure is easy and has excellent test–retest reliability (*r* = 0.905) [50] and good concurrent validity reliability (*r* = 0.75) with GAITRite system [53]	Baseline 4th week 8th week 20th week
8	Motor function (lower limb)	It will be measured with the use of the Motricity Index by assessing hip flexion, knee extension and dorsiflexion in sitting position. The strength of the lower limb will be rated as 0 (no movement); 9 (palpable contraction in muscle, but no movement); 14 (visible movement, but not full range and not against gravity); 19 (full-range movement against gravity, but not resistance); 25 (full movement against gravity, but weaker than the other side); and 33 (normal power) For the hip flexion test, while sitting on a chair, with the paretic hip bent at 90°, the participants will be asked to move the knee towards the chin and the examiner then monitors the contraction of iliopsoas/rectus femoris (anterior thigh). (14 points will be given if there is less than a full range of passive motion; 19 points will be given if the hip is fully flexed yet it can be easily pushed down). For the knee extension test, participants will be asked to sit on a chair with their foot unsupported and the knee at 90°. The examiner will then monitor the contraction of the quadriceps (14 points will be given for less than 50% of full extension; 19 points will be given for full extension yet it can be easily pushed down). For the ankle dorsiflexion test, it will be tested with the foot relaxed in a plantarflexed position. The participant will be asked to dorsiflex the foot and the examiner monitors the tibialis anterior (14 points will be given if there is less than a full range of dorsiflexion)	It is easy to administer and has high inter-rater reliability (*r* = 0.87) and validity (*r* = 0.81 *vs* Rivermead Motor Assessment) for measuring leg impairment in chronic stroke patients [54]	Baseline 4th week 8th week 20th week

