Post-stroke abnormal gait patterns contribute to significant functional disability, impaired walking ability and poor quality of life [20]. Gait asymmetry implies an imbalance in functional activities between two sides of the body or lower limb [21]. Post-stroke hemiparetic gait is caused by motor impairments such as altered muscle tone, lack of selective motor control, abnormal reflex, poor balance and weakness [22]. Asymmetrical spatial and temporal gait characteristics are common deviations observed in post-stroke hemiplegic gait. It has been documented that about 44–62% and 48–82% of stroke survivors exhibit asymmetry in spatial and temporal gait parameters, respectively [23, 24].

Observational studies have shown that post-stroke hemiparetic gait relative to the normal is significantly characterised by short step length and stride length, reduced cadence, low gait speed, increased step width, double support phases and asymmetric single limb loading [25–28]. After stroke, the paretic limb exhibits a prolonged period of swing and a reduced period of stance; as a result, decreased swing time and increased stance time are seen on the non-paretic limb [29]. These changes are believed to result from decreased walking speed as well as disturbances in other gait parameters between the paretic and non-paretic limbs which may limit gains from rehabilitation [30].

Gait asymmetry does not only affect gait quality in stroke but may also increase energy expenditure [31] and risk of falls [32] and causes loss of bone density of the hemiparetic lower limb [33]. Restoring gait symmetry is, therefore, a major goal for rehabilitation to enhance walking ability and safety, activities of daily living and quality of life among stroke survivors [34].

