#### Measurement of spatial gait parameters

The spatial gait parameters of the participants in both groups will be recorded using the footprint method as described by previous publications [55–57]. Footprints provide a simple and economical method from which step length, stride length, foot angle and stride width can be measured. While sitting on the chair, a pair of flat shoes (slippers) will be given to the participant to wear. Different sizes will be provided to the participants to suit their foot size. All the shoes will be provided with a strap that will be tied to the affected heel to avoid missing steps during the gait training. Ink paste will be applied at the bottom of the participant’s shoes. They will be then asked to stand and walk with the instruction “walk as you normally do” across the 10-m path (as described in the procedure for overground walking training) and footprint sequences from the ground surface will be recorded. The participants will be asked to look directly forward during walking as observing the footprints could alter their gait patterns. At least six footprints will be obtained. The first few steps of the gait footprints will be disregarded because they may not be indicating the stable gait of the participants. Spatial gait parameters will be measured from the footprints using a measuring tape for each of the selected gait components. Each participant will perform three trials of walking and the spatial gait parameters will be recorded in each trial; the average will be then computed. The measurements will be recorded to the nearest centimeters for both the loaded paretic lower limb and non-loaded paretic lower limb during the overground training (Fig. 3). All the parameters will be measured and recorded separately for each leg. The ground floor will be cleaned and mopped to be cleared for the next participant. The spatial gait parameters and symmetry to be measured are fully described in Table 2.

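### The stride length symmetry ratio is about 1 by geometry, and the signed step length symmetry ratio can hide or reverse a real gain in symmetry if participants lie on both sides of 1

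*Protocol article*

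**What the plan says.** Table 2 of the protocol article lists both ratios as secondary outcomes. Item 3, step length symmetry ratio: "It will be calculated by dividing the step length of the paretic limb to that of the non-paretic limb". Item 5, stride length symmetry ratio: "It will be calculated by dividing the stride length of the paretic limb to that of the non-paretic limb". Neither is folded, logged or expressed as a distance from 1, and no direction of benefit is given. The table supports item 3 with a citation recommending the calculation. The psychometrics cell for item 5 is empty.

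The lengths behind the ratios are also defined in Table 2. A step is "the distance from the heel strike of one foot to the heel strike on the next successive step of the opposite foot". A stride is obtained by "measuring the linear distance from the heel strike of one foot to the heel strike of the next successive step of the same foot".

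Under Measurement of spatial gait parameters, "All the parameters will be measured and recorded separately for each leg", and "At least six footprints will be obtained" in each of three averaged walks. The first few steps are discarded. The walk follows the straight taped 10-m path described under Study interventions.

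Statistical analysis puts every primary and secondary outcome into the same linear mixed model and takes the adjusted between-group difference as the treatment effect. For these two items that is a difference in mean ratio.

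**The concern.** The Background names restoring gait symmetry as a major rehabilitation goal, and these two items are the trial's only symmetry outcomes.

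Perfect symmetry is a ratio of 1. A participant at 0.75 improves by going up, and one at 1.333 improves by going down. A difference in mean ratio therefore has no consistent direction of benefit, and opposite gains offset each other. The eligibility criteria under Participants' recruitment neither require asymmetry nor restrict its direction. The Background gives only its frequency ("44–62% and 48–82% of stroke survivors exhibit asymmetry in spatial and temporal gait parameters, respectively").

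The stride ratio has a different problem. A quantity that is the same on both legs by construction cannot register asymmetry, so a null result on it could be misread as evidence that symmetry did not change.

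**Working it through.** The plan states no figure for either ratio, so there is none to reproduce. The arm sizes used below, 21 and 24, come from Sample size calculation (42 before dropout, 48 after).

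**1. Stride ratio, steady gait.** Let P and N be the paretic and non-paretic step lengths. Two successive heel strikes of the same foot enclose one step of each leg, so:

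- paretic stride = N + P
- non-paretic stride = P + N
- stride ratio = 1

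| P / N (cm, illustrative) | Step ratio | Stride, each leg (cm) | Stride ratio |
|---|---|---|---|
| 30 / 50 | 0.60 | 80 | 1.000 |
| 40 / 40 | 1.00 | 80 | 1.000 |
| 50 / 30 | 1.67 | 80 | 1.000 |

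**2. Stride ratio, step-to-step noise.** Take six alternating footprints at x1 to x6.

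- One leg's mean stride is (x5 − x1)/2 and the other's is (x6 − x2)/2.
- Their difference is [(x2 − x1) − (x6 − x5)]/2. This is half the difference between the first and last recorded steps, which belong to the same leg, so the paretic/non-paretic contrast drops out.
- With an assumed step SD of 3 cm, the variance per walk is 2 × 9/4 = 4.5 cm², and over three walks 1.5 cm².
- Rounding both means to the centimetre adds 2 × 1/12 = 0.167 cm².
- SD of the ratio = √1.667 / 80 = 0.016.

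Simulation of the three gaits above gave means of 0.999 to 1.000 and an SD of 0.016 in each. What varies is measurement and step noise.

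**3. Step ratio, arithmetic.** Assume baseline ratios of 0.75 (a share q of participants) or 1.333 (the rest), and that treatment halves each deviation from 1.

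- Below 1: 0.75 → 0.875, a change of +0.125.
- Above 1: 1.333 → 1.167, a change of −0.167.
- Mean signed change = 0.125q − 0.167(1 − q), which is zero at q = 0.1667/0.2917 = 0.57.
- Folded (larger/smaller): 1.333 → 1.143 or 1.167, a fall of 0.19 or 0.17.

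| Share below 1 | Mean signed change | Mean folded change |
|---|---|---|
| 100% | +0.125 | −0.190 |
| 90% | +0.096 | −0.188 |
| 70% | +0.037 | −0.183 |
| 60% | +0.008 | −0.181 |
| 50% | −0.021 | −0.179 |
| 0% | −0.167 | −0.167 |

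Every treated participant improves in every row.

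**4. Step ratio, power.** These are t-tests on change at alpha 0.05. Treatment halves asymmetry and everyone is asymmetric. All gait inputs are assumed.

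- Setting A: 21 per arm, mean absolute log ratio 0.30 (SD 0.12), log noise 0.06.
- Setting B: 24 per arm, mean absolute log ratio ln(1/0.75) = 0.288 (SD 0.08), log noise 0.10.

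| Share below 1 | Signed, A | Signed, B | Folded, A and B |
|---|---|---|---|
| 50% | 11% | 11% | over 99% |
| 60% | 5% | 5% | over 99% |
| 70% | 12% | 12% | over 99% |
| 80% | not run | 35% | over 99% (B only) |
| 90% | 72% | 73% | over 99% |
| 100% | over 99% | over 99% | over 99% |

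**5. Fewer asymmetric participants.** Setting A was rerun with only 44–62% asymmetric, the Background's range for spatial parameters, and the rest near 1 (assumed log SD 0.03).

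- Halving: folded or absolute-log power is about 67–90%. Signed power is about 5–9% at 50–70% below 1.
- A 25% reduction instead: folded power is about 31–48%. If everyone is asymmetric it is about 78%.

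**The case against.** **Direction.** The strongest reply is that cancellation needs participants on both sides of 1, and the documents do not show that they will be. This stands. The absence of a restriction on direction does not establish a mixed sample. A reader might infer that neither symmetry outcome can show improvement. For the step ratio that is not supported, because it performs well when nearly everyone lies on one side.

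**Size of the gain.** A reader might also take the folded measure to have power above 99% in general. That holds only when everyone is markedly asymmetric and treatment halves the asymmetry; with the Background's frequencies it is lower. The simulations also use a two-time-point t-test and not the four-assessment mixed model. Even so, the folded measure matched or beat the signed ratio in each setting examined, to within simulation error.

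**Rationale for the signed ratio.** Table 2 cites a recommendation for it, only the paretic limb is loaded, and the signed form shows which leg changed. These are good reasons to keep reporting it. They do not stop opposite gains cancelling in a group mean. An analysis plan that is not shown could specify a folded form, but the definition that the protocol fixes is unfolded.

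**Consequence.** Step length and gait speed, the primary outcomes, are untouched. That the trial would present the stride ratio as evidence on symmetry is a risk, since nothing in the documents says how it will be interpreted.

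Nothing in the documents answers the stride point.

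**Conclusion.** The stride part holds in full and needs no assumption about the direction of asymmetry. In steady straight walking the ratio is 1.000 for step ratios from 0.60 to 1.67, with an SD of about 0.016 under an assumed 3 cm step SD. A between-group difference in it says nothing about step symmetry.

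The step part holds conditionally. With baseline ratios of 0.75 and 1.333 and asymmetry halved in everyone treated, the mean signed change vanishes at about 57% below 1 and has the opposite sign at 50%. Signed-ratio power runs from about 5–12% (50–70% below 1) through about 70% (90%) to over 99% (100%). These figures rest on assumed gait values and an assumed treatment effect. The deciding quantity, the share of participants on each side of 1, is neither restricted nor reported.

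The plan should be changed, but this is a matter of how two secondary outcomes are defined and does not bear on the primary comparison.

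**What to change.** By documented amendment, before any comparison by arm:

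- **Step length symmetry:** analyse the absolute log of paretic over non-paretic step length (or larger over smaller step) as the symmetry outcome, with lower values meaning better symmetry. Report the signed ratio alongside it to show direction.
- **Stride length ratio:** keep it only as a measurement check with no inference on symmetry, or remove it. Keeping it relabelled is the less disruptive choice.

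Cost: no new data are needed, because each leg is already recorded separately. The step outcome is a recomputed variable. Changing the status of a listed secondary outcome means notifying the ethics committee and updating the registry, as Trial status and amendments already provides. The folded measure does not show which leg is longer, which the signed ratio covers, and it is skewed, so model residuals should be checked. The choice should be fixed in advance, since picking the metric after seeing results by arm would be data-driven.
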